### Demographic information

Data to be collected include age, gender, marital status, age of any children, postcode, occupation and education level.

### Medical records

Data will include cancer type, stage, treatment, time since diagnosis, treatment outcomes, recurrence, treatment side-effects/toxicities, performance status, other non-cancer morbidities, unscheduled/emergency appointments at treating centre and other identified centres, admissions as an inpatient, addition to or changes in medication prescriptions to manage toxicities and referrals to allied health services at the treating centre.

### Psychological distress

The *Brief Symptom Inventory 18 (BSI-18)* was selected as the primary outcome measure [24]. It comprises 18 items answered on a 5-point scale to score global distress. Subscales assess anxiety, depression and somatisation. It has demonstrated reliability, validity, acceptability and responsiveness and has been used extensively in both cancer and general populations. It has been recommended for use in identifying psychological distress in a clinical setting [25]. The *Distress Thermometer (DT)*[26] is a reliable and valid single item measure of distress in cancer populations, which appears responsive to change [27].

### Survivors unmet needs

*Cancer Survivors’ Unmet Needs measure (CaSUN)*[28] will be used to assess survivors’ unmet needs. It includes 35 unmet need items, 6 positive change items and an open-ended question. The scale has good acceptability, internal consistency and validity. A review of measures of survivors’ unmet needs suggests that the CaSUN performs as well, or better, than any other measure [29].

### Quality of life

The European Organisation for Research and Treatment of Cancer core questionnaire (EORTC QLQ C-30) [30] will be used together with the colorectal cancer module (EORTC QLQ CR-29) [31] to measure quality of life. Together, the scales include 59 items that assess quality of life issues specific to this patient group. The measures are widely used, with good test-retest reliability, validity, responsiveness and acceptability.

### Sample size requirements

The primary outcome for this longitudinal randomised controlled trial is psychological distress as assessed by the BSI-18 Global Severity Index, an 18-item scale with a possible range of 72. The BSI-18 will be completed once at baseline and twice post-intervention, but the main contrast of interest is the difference between arms at the first post-intervention follow-up.

In this case, we based our sample size calculations on 80% power, a two-sided *t*-test with an alpha-level of 0.05, a difference between groups of 3.6 points on the primary outcome (or 5% of the instrument range) [32] and a standard deviation of 8.6 [24] (a standardised difference of 0.42). Given these specifications, the required sample size is 180 patients (or 90 patients per arm). Assuming attrition of up to 10%, 200 patients will need to be recruited (or 100 patients per arm). Furthermore, assuming an 80% recruitment rate, approximately 250 patients will need to be approached to achieve a total sample of 200 patients. Patients will be recruited over 24 months.

### Statistical analysis

Analyses will be by intention-to-treat and performed in SPSS Windows Version 21.0 (or higher) (Chicago, IL, USA). Prior to formal analyses, descriptive statistics and graphical displays will be used to identify missing and out-of-range values, assess the distributional characteristics of test scores and summarise study measure completion rates and missing data points. Responses to the BSI-18, DT, CaSUN, EORTC QLQ C-30 and CR-29 will be scored according to algorithms in the users’ manuals for these instruments.

Descriptive statistics will be used to summarise baseline demographic and clinical characteristics of patients randomised to the intervention and usual care. Recruitment bias and possible differential attrition will be assessed by comparing basic demographic and clinical characteristics of responders and non-responders, as well as drop-outs and continuing participants, using *t*-tests (or Mann–Whitney U) and chi-squared tests as appropriate.

Primary and secondary outcome analyses will be carried out by fitting a linear mixed model to each outcome separately using all available data. A cell means model will be used to estimate mean scores for each group by time combination. An unstructured covariance type will be used to model the covariance structure among repeated measures and all models will be estimated by maximum likelihood. Group comparisons at post-baseline time points will be performed using contrasts within the proposed models. After inspection of the data, the appropriateness of stated methods will be revised, if necessary. Because of the number of significance tests for secondary outcomes, Hochberg’s modified Bonferroni procedure will be used so that the overall type I error rate does not exceed 0.05 [33].

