### Study hypotheses

#### Primary endpoint

CRC survivors allocated to the SurvivorCare intervention will report a significant relative benefit for psychological distress compared to survivors in the control group from baseline to Follow-up 1 (eight weeks after randomisation for the usual care group, and eight weeks after the first intervention session for the SurvivorCare group).

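### The Follow-up 1 comparison makes no use of the baseline BSI-18 already collected; adjusting for it would be a free gain in precision, and the hypothesis wording should name the same contrast

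*Protocol article*

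**What the plan says.** All four statements are in the protocol article.

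- **Statistical analysis, model:** each outcome gets its own linear mixed model with unstructured covariance, estimated by maximum likelihood. On the mean structure: "A cell means model will be used to estimate mean scores for each group by time combination".
- **Statistical analysis, test:** "Group comparisons at post-baseline time points will be performed using contrasts within the proposed models". No baseline covariate is listed, and no constraint on the baseline means is stated.
- **Sample size requirements:** "the main contrast of interest is the difference between arms at the first post-intervention follow-up". The calculation is a two-sided *t*-test with 80% power, alpha 0.05, SD 8.6 and "a difference between groups of 3.6 points on the primary outcome (or 5% of the instrument range"). The result is 90 per arm, raised to 100 for up to 10% attrition.
- **Primary endpoint (hypotheses):** SurvivorCare patients "will report a significant relative benefit for psychological distress compared to survivors in the control group from baseline to Follow-up 1".

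Table 2 (Data collection procedure) has the BSI-18 completed at baseline, on the day of randomisation, and at both follow-ups.

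**The concern.** A mixed model that includes baseline as one of its repeated outcomes can look as if it adjusts for baseline. It does not do so when each arm has its own baseline mean, which is the natural reading of a mean for every group-by-time cell. In that model, with complete data, the estimated Follow-up 1 difference is the raw difference in means, and the correlation with baseline does not improve it. The trial collects a baseline value of the primary outcome and then leaves it out of the primary comparison. What is at stake is precision, for the primary outcome and for each secondary outcome analysed in the same way.

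A smaller matter goes with it. The hypothesis can be read as a between-arm difference in change from baseline, while the sample size section names the between-arm difference at Follow-up 1. Both contrasts have the same expected value under randomisation, but they have different standard errors and can give different p-values on the same data. One wording should serve throughout.

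**Working it through.** **Inputs from the article (Sample size requirements):** difference 3.6 (5% of 72 = 3.6), SD 8.6, two-sided alpha 0.05, power 80%, 90 per arm.

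**Assumption:** the correlation rho between baseline and Follow-up 1 BSI-18. The article gives none, so a range of 0.3 to 0.7 is shown. For the change contrast and the imbalance figures, the SD is also taken as 8.6 at both times.

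**1. The plan's own figure.** n per arm = 2 × [8.6 × (1.960 + 0.842) / 3.6]² = 89.6, so 90. Power of the *t*-test at 90 per arm is 79.8% (80.2% by the normal approximation). The stated sample size reproduces. It belongs to the unadjusted Follow-up 1 difference, with SE = 8.6 × √(2/90) = 1.28, and does not depend on rho.

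**2. Does the planned model adjust for baseline?** One complete dataset was simulated (90 per arm, SD 8.6, rho 0.6) and fitted by generalised least squares with the covariance taken as known. The chance baseline difference in it was −1.085.

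| Mean structure | Follow-up 1 difference | SE |
|---|---|---|
| Raw difference in means | −4.130 | – |
| Separate mean in every group-by-time cell | −4.130 | 1.282 |
| Common baseline mean | −3.479 | 1.026 |

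The cell-means contrast equals the raw difference. The common-baseline estimate is the raw difference less rho times the baseline difference: −4.130 − 0.6 × (−1.085) = −3.479. With about 10% of patients losing both follow-ups, the SEs were 1.306 and 1.055, so the gap remains.

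**3. Size of the gain.** The baseline-adjusted SE is 1.28 × √(1 − rho²). Power is from the *t*-test at 90 per arm, difference 3.6.

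| Assumed rho | √(1 − rho²) | Adjusted SE | Power, adjusted | Power, unadjusted Follow-up 1 (as planned) | Power, difference in change |
|---|---|---|---|---|---|
| 0.3 | 0.954 | 1.22 | 83% | 80% | 66% |
| 0.4 | 0.917 | 1.17 | 86% | 80% | 72% |
| 0.5 | 0.866 | 1.11 | 90% | 80% | 80% |
| 0.6 | 0.800 | 1.03 | 94% | 80% | 88% |
| 0.7 | 0.714 | 0.92 | 97% | 80% | 95% |

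The last column uses SD × √(2(1 − rho)). It equals the planned contrast at rho 0.5 and lies below the adjusted contrast throughout this range.

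**4. Chance imbalance.** The SE of the baseline difference is also 1.28, so its 95% range is ±1.96 × 1.28 = ±2.5 points. At rho 0.6 this carries ±0.6 × 2.5 = ±1.5 points into the unadjusted estimate. That variation is already part of the unadjusted SE of 1.28. It explains where the precision in step 3 comes from and is not a further loss.

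**The case against.** **The planned comparison is sound.** Comparing arms at follow-up is valid under randomisation, has no bias in expectation, does not inflate the type I error, and is the contrast the trial was sized for. This stands, which is why the point is offered as an improvement.

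**The article is condensed, and covariates are often left to the analysis plan.** This stands in part. The word unconstrained is inferred and not written. But the article does state a mean structure, and a mean for each cell gives each arm its own baseline mean. The proposal therefore replaces a stated method and does not merely fill in a missing detail.

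**The contrast is already named.** This largely stands. The sample size section names the Follow-up 1 difference, and the analysis section's post-baseline group comparisons agree with it. The hypothesis may simply describe the period over which benefit is expected. What remains is a wording alignment.

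Two stronger conclusions are tempting, and the article does not support either.

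- A reader might infer that the trial is underpowered. That needs both the change reading of the hypothesis, against the contrast named in the sample size section, and a correlation below 0.5, which the article does not give.
- A reader might infer that baseline imbalance passes in full into the result and adds to the loss of precision. It is scaled by rho and is already inside the unadjusted SE, so it is the same cost and not a second one.

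Replacing maximum likelihood is not worth asking for either. With 180 complete cases in two arms, the SE would change by a factor of about √(178/180), or 0.6%.

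**Conclusion.** The point holds as a free improvement, not as an error in the sample size or a source of bias. As described, the primary comparison is the unadjusted Follow-up 1 difference, with SE 1.28 and the stated 80% power at 90 per arm. Adjustment for baseline would reduce the SE by about 5% at rho 0.3 and 20% at rho 0.6, taking power to about 83% and 94%. These gains rest on the assumed correlation. The reading of the model rests on the absence of any stated baseline covariate or constraint. The sample size can stay as it is, and it becomes conservative under adjustment. The hypothesis and the sample size section need one agreed wording for the primary contrast.

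**What to change.** - **Statistical analysis:** either enter baseline BSI-18 as a covariate with Follow-up 1 and Follow-up 2 as the outcomes, or keep baseline as an outcome and constrain its mean to be equal in the two arms. Name the Follow-up 1 group difference from that model as the single primary contrast.
- **Baseline timing:** state that the adjustment uses a baseline questionnaire completed before allocation is disclosed. The Data collection procedure section places it on the day of randomisation without giving the order, and both forms of adjustment need a baseline that knowledge of the arm cannot have affected.
- **Secondary outcomes:** do the same for each, with its own baseline.
- **Primary endpoint and Sample size requirements:** reword the hypothesis so that both sections name the baseline-adjusted Follow-up 1 difference.

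The cost is analysis wording, plus confirming the order of baseline completion and disclosure. No new measures, larger sample or different software is needed. Recruitment is described as open, so the change can be settled before analysis.

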## Methods

### Design and setting

The study is being undertaken at 18 sites within Australia. Peter MacCallum Cancer Centre is the coordinating site, with all participant data stored centrally. A feasibility survey was conducted in January 2009. Sites were selected based on their proximity to patients in addition to the availability of at least one nurse to administer the SurvivorCare intervention. Ideally, the nurse would be a specialist colorectal cancer nurse; however, nurses with general oncology experience were also eligible. Availability of site resources/space to conduct the study was also considered.

Ethical approval was obtained individually by the Human Research Ethics Committees of Victorian and Tasmanian sites, and a central governance approval was obtained for all sites in New South Wales.

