### Intervention staff training

Intervention nurses with experience looking after people with bowel cancer have been trained to provide the end of treatment and telephone follow-up sessions at each site. An expert in communication skills training and two experts in nurse-led clinics and self-care education conducted a full-day training program comprising: (a) an overview of the project, emphasising prevention of diffusion of the intervention at the site; (b) explanation of how to use the intervention manual; (c) training in eliciting and responding to emotional cues, including dealing with distress; (d) instruction on exploring concerns and providing evidence-based advice; (e) instruction in how to effectively facilitate referral to multidisciplinary team members; (f) instruction on how to coach patients to use evidence-based strategies; (g) role-play with simulated patients (actors) and activity sessions to practice the intervention, including self-appraisal and constructive feedback.

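### The sample size and the stated mixed model ignore grouping by delivering nurse and by site; the direction of the error depends on nurse and site variation that the protocol does not quantify

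*Protocol article*

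**What the plan says.** All references are to the protocol article.

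- **Delivery.** Under Design and setting, the 18 sites were chosen partly for "availability of at least one nurse to administer the SurvivorCare intervention"; specialist colorectal nurses were preferred, but general oncology nurses could also take part. Under Intervention staff training, nurses "have been trained to provide the end of treatment and telephone follow-up sessions at each site". The total number of nurses is not given.
- **Control arm.** The Usual care section withholds the nurse-led sessions from controls. Study integrity and quality assurance foresees sites where a single nurse serves both arms.
- **Allocation.** Recruitment process describes 1:1 allocation, balanced by site through minimisation.
- **Sample size.** The calculation uses a t-test, two-sided at the 5% level, with a power target of 80%. The effect sought is "a difference between groups of 3.6 points on the primary outcome"; for the spread of scores the plan takes "a standard deviation of 8.6". It concludes that "the required sample size is 180 patients (or 90 patients per arm"). No design effect is applied.
- **Analysis.** The Statistical analysis section sets out group-by-time cell means, and for the correlation: "An unstructured covariance type will be used to model the covariance structure among repeated measures". Neither nurse nor site appears in the model. The section also allows the methods to be revised after the data have been inspected.

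**The concern.** The nurse is a large part of the treatment: a tailored face-to-face session of 60 to 90 minutes, then three calls. If some nurses obtain better results than others, outcomes of patients who share a nurse are correlated. This happens mainly in the SurvivorCare arm, so the design is partially nested. An unstructured covariance across one patient's three assessments cannot represent correlation between patients.

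Site raises a second issue. Allocation is balanced by site, so a site effect common to both arms largely cancels from the treatment contrast. A model without site still counts that variation as noise.

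The validity of the primary test and the meaning of the 80% power figure are at stake. The secondary outcomes use the same model and are affected in the same way.

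**Working it through.** **1. The plan's own figure.** Inputs from Sample size requirements: difference 3.6, SD 8.6, two-sided alpha 0.05, power 80%.

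- d = 3.6/8.6 = 0.4186.
- n per arm = 2(1.960 + 0.842)²/d² = 89.6, rounded up to 90. This matches the plan.
- Power at 90 per arm is 80.2% by the normal approximation and 79.8% by the noncentral t.
- 180/0.9 = 200 recruited, which also matches.

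The stated size is therefore correct if patients are independent.

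**2. Nurse clustering in one arm.** Assumptions, none of them in the document: k nurses with equal caseloads, m = 90/k analysed SurvivorCare patients per nurse, nurse ICC ρ, no site effect.

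- Design effect in the SurvivorCare arm: DE = 1 + (m − 1)ρ.
- Variance factor for the contrast: f = (DE + 1)/2, because the control arm keeps a factor of 1.
- Type I error of the planned test (uncorrected SE): 2[1 − Φ(1.96/√f)].
- Power of a test with the correct SE: noncentral t power at d/√f, 90 per arm.

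| Nurses (m) | ρ | DE | f | True SE / model SE | Type I error, planned test | Power, corrected test |
|---|---|---|---|---|---|---|
| 18 (5) | 0.01 | 1.040 | 1.020 | 1.010 | 5.2% | 79.0% |
| 18 (5) | 0.05 | 1.200 | 1.100 | 1.049 | 6.2% | 75.9% |
| 18 (5) | 0.10 | 1.400 | 1.200 | 1.095 | 7.4% | 72.2% |
| 36 (2.5) | 0.05 | 1.075 | 1.0375 | 1.019 | 5.4% | 78.3% |

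The last two columns describe different tests. The planned test, with its SE too small, also rejects more often when the effect is real. Its power is approximately Φ[(2.808 − 1.96)/√f], where 2.808 = d√45. With 18 nurses this gives 80.0%, 79.1% and 78.1% at ρ = 0.01, 0.05 and 0.10.

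**3. Adding a site effect shared by both arms.** Let s be the share of variance due to site, with allocation exactly balanced within site. The site part cancels from the contrast, but the model still counts it. With k = 18 and m = 5:

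f = ½[mρ + (1 − s − ρ) + (1 − s)] = 1 + 2ρ − s.

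| Nurse ρ | Site s | f | True SE / model SE | Type I error, planned test |
|---|---|---|---|---|
| 0 | 0.05 | 0.95 | 0.975 | 4.4% |
| 0.02 | 0.05 | 0.99 | 0.995 | 4.9% |
| 0.05 | 0.05 | 1.05 | 1.025 | 5.6% |
| 0.05 | 0.10 | 1.00 | 1.000 | 5.0% |

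The two omissions pull in opposite directions, and the net sign depends on values that the article does not give.

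**The case against.** A reader might infer that the SE is certainly too small and that the planned test combines a type I error of 6% to 7% with power of 72% to 76%. The documents do not support either inference. The first needs a nurse effect that outweighs any shared site effect. At sites where one nurse serves both arms, part of the nurse effect is itself shared. The second joins the error rate of the uncorrected test to the power of the corrected one.

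The size also rests on assumed values. One nurse at each of 18 sites is the fewest possible if every site has its own nurse, and more nurses shrink the effect. Unequal caseloads would enlarge it: with a caseload coefficient of variation of 0.6, 18 nurses and ρ = 0.05, the type I error is 6.7%. The manual, common training and review of taped sessions are all meant to make delivery uniform, so ρ may be small. At ρ of 0.01 to 0.02 with equal caseloads, the loss of power is only one to two points.

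Finally, a journal article is condensed, and a nurse or site term might sit in an unseen analysis plan. That carries some weight. Still, the article does specify fixed effects, covariance and estimation method, and it gives a sample size with no allowance for clustering. A general right to revise methods after seeing the data does not replace a prespecified term. The possible cancellation between nurse and site effects is no defence either, because it needs two unknown quantities to match.

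**Conclusion.** The point holds in conditional form. Both the sample size and the stated model treat patients as independent, although SurvivorCare patients are grouped by nurse and allocation is balanced by site. If nurses differ, the SE of the primary contrast is too small; if sites differ in a way common to both arms, it is too large.

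With 18 nurses, equal caseloads and no site effect, ρ from 0.01 to 0.05 raises the type I error of the planned test to between 5.2% and 6.2%. A test that allows for the clustering then has power between 79% and 76%. With 36 nurses and ρ = 0.05 the figures are 5.4% and 78%. The sample size of 180, or 200 recruited, is arithmetically right on its stated basis. The effect is modest, but it touches every contrast and is cheap to deal with while recruitment is open.

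**What to change.** 1. Record the delivering nurse for each SurvivorCare patient.
2. Prespecify site in the model, since it already enters the minimisation, together with a nurse random effect present only in the SurvivorCare arm, with small-sample degrees of freedom such as Satterthwaite. The two terms belong together. Where nurse and site coincide, a nurse term alone absorbs shared site variance and overcorrects: in simulation, type I error fell to between 2.8% and 3.8% at site ICC 0.05 to 0.10.
3. In Sample size requirements, state that 80% power assumes no nurse clustering, and show the range of power under a declared ICC and number of nurses. A single replacement figure would not be justified.
4. If baseline adjustment is offered as a way to regain power, make that conditional on the assumed correlation between baseline and follow-up scores. It does not repair an understated SE.

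The cost is one data field, two model terms and a few sentences. No extra patients are needed. The interval may be wider, and the nurse variance will be estimated imprecisely from about 18 small clusters.

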## Discussion

CRC survivors represent a large and rapidly growing group of people. It is critical that their serious and often distressing needs following treatment completion are appropriately managed. Unfortunately, there are few interventional studies that seek to improve psychosocial and supportive care outcomes for cancer survivors and the investigators identified no studies for patients with CRC, following treatment completion.

This study will examine the impact of a nurse-led intervention package for CRC survivors using important clinical outcomes, such as distress, anxiety and depression, as well as unmet needs and quality of life. SurvivorCare recognises treatment completion as a critical period. The intervention is patient-centred, individually tailored and nurse-led with active GP engagement. It screens for distress, provides evidence based information and coaching in self-care and stress reduction. Patients are offered health promotional strategies and, where appropriate, referred to a broader multidisciplinary team. The effectiveness of the intervention will be assessed in terms of important clinical outcomes, specifically distress, anxiety and depression, unmet needs and quality of life.

SurvivorCare has the potential to considerably reduce individual suffering, but it is also likely to reduce the cost of health provision to this group of patients, as failing to meet patients’ psychological and supportive care needs results in longer hospital stays and higher medical costs [34]. If the intervention is successful in achieving the expected health benefits, it could be disseminated readily. Furthermore, the intervention could easily be adapted to other cancer or chronic disease settings. By encouraging consumer involvement in health care planning and promoting shared care between specialist treatment centres and community services, the proposed research program has the potential to transform health care practices.

